## Abstract

**Introduction:**

Adolescence is a critical period for youths with chronic conditions, when they are supposed to take over the responsibility for their health. Type 1 diabetes (T1D) is one of the most common chronic conditions in childhood and inadequate self-management increases the risk of short-term and long-term complications. There is a lack of evidence regarding the effectiveness of transition programmes. As a part of the Swedish Transition Effects Project Supporting Teenagers with chrONic mEdical conditionS research programme, the objective of this study is to evaluate the effectiveness and experiences of different transitional care models, including a person-centred transition programme aiming to empower adolescents with T1D to become active partners in their health and care.

**Methods and analysis:**

In this randomised controlled trial, patients are recruited from two paediatric diabetes clinics at the age of 16 years. Patients are randomly assigned to either the intervention group (n=70) where they will receive usual care plus the structured transition programme, or to the control group (n=70) where they will only receive usual care. Data will be collected at 16, 17 and 18.5 years of age. In a later stage, the intervention group will be compared with adolescents in a dedicated youth clinic in a third setting. The primary outcome is patient empowerment. Secondary outcomes include generic, diabetes-specific and transfer-specific variables.

**Ethics and dissemination:**

The study has been approved by the Ethical Review Board in Stockholm (Dnr 2018/1725-31). Findings will be reported following the Consolidated Standards of Reporting Trials statement and disseminated in peer-reviewed journals and at international conferences.

**Trial registration number:**

NCT03994536

Strengths and limitations of this studyThe evidence of transition interventions targeting different long-term conditions is still insufficient; this study will expand current knowledge on transitional care.Experience from an ongoing project where the person-centred transition programme is evaluated in another group of adolescents with long-term conditions assures study fidelity.Blinding of participants is not possible.Long-term follow-up of the effectiveness of transition interventions is important and desirable. Although not included in this study, prolonged follow-up is needed.

## Introduction

Worldwide, nearly 132 600 000 children and adolescents under 20 years develop type 1 diabetes (T1D) each year. The annual mean incidence rate varies from 0.1–60 to 100 000, with Sweden as one of the ‘top’ incidence countries.^1^ Children with T1D need lifelong medical follow-up to prevent acute and long-term complications. The lifelong follow-up will comprise a shift in care when adolescents are transferred from a paediatric to adult care services. Simultaneously, there is a shift in roles between parents and adolescents, where the adolescent needs to start taking over the responsibility for their health and care. Furthermore, this shift occurs during a vulnerable developmental period, when adolescents are exposed to unique challenges.^2 3^ A smooth transition to adulthood and well-timed and planned transfer to adult care allows adolescents to optimise their ability to assume adult roles and functioning, which can improve medical outcome.^4^ In this article, transfer is defined as the actual event when adolescents move from a paediatric to adult care services, while transition is defined as the process by which they become prepared to take charge of their lives and their health in adulthood.^5^

Transition programmes for adolescents with chronic conditions aim to prepare and support them during the transition to adulthood and transfer to adult care so that they can gradually become active partners in their health and care. In this respect, adequate self-management and participation in care are essential and it is of utmost importance that patients feel empowered.^6^ Patient empowerment is a critical attribute of person-centred care (PCC) and highlights the importance of knowing the person behind the patient.^7^ Patient empowerment is considered to be *‘*An enabling process or outcome arising from communication with the healthcare professional and a mutual sharing of resources over information relating to illness, which enhances the patient**’**s feelings of control, self-efficacy, coping abilities and ability to achieve change over their condition*’*.^8^ Research on the application of patient empowerment in adolescent health and transitional care is limited. The application of PCC principles in young persons with chronic diseases is unprecedented, although there is a growing demand for PCC in diabetes care. Moreover, research on transition and transfer and on interventions that have the potential to improve both processes is important. Nevertheless, evidence on the effectiveness of transition programmes using a randomised controlled trial (RCT) is sparingly reported.^9^ Evidence base for interventions that improve outcomes for this specific target group is limited and not adequate in guiding clinical practice to support better self-management and outcomes in youths with T1D.^10^

It is known from previous studies that transfer from paediatric to adult care services is associated with deterioration in health of adolescents with certain chronic conditions.^9^ For adolescents with T1D, this includes non-optimal glycaemic control and increased diabetes related hospitalisations after transfer, as well as general patient dissatisfaction with the transition experience. Poor clinic attendance after transfer is considered a risk factor.^11 12^ Potential importance of continuity of care, support, education and individualised support is highlighted across different types of interventions targeting young persons with T1D.^13^ Within diabetes care, healthcare professionals agree that a lack of an effective and structured transfer from paediatric to adult care may contribute to insufficient continuity of healthcare and increased risk of adverse outcomes in young adults with T1D.^14 15^

To investigate the effectiveness of a structured person-centred transition programme for adolescents with chronic conditions, the Swedish Transition Effects Project Supporting Teenagers with chrONic mEdical conditionS (STEPSTONES) has been established. STEPSTONES is a research project in which a transition programme has been developed and currently tested in an ongoing RCT in adolescents with congenital heart disease (CHD).^16 17^ Theoretical framework for the transition programme is supported by the conceptualisation of empowerment defined by Small *et al*^8^ and with other attributes related to the concept. The components are following the philosophy of PCC,^7^ operationalised and guided by several change theories/models described by Acuña Mora *et al*.^18^ The STEPSTONES transition programme is generic in nature and can therefore be expanded to other childhood-onset conditions, such as T1D.

### Objectives and hypothesis

The overall objective of STEPSTONES-DIAB is to evaluate the effectiveness of transitional care, aiming to empower adolescents with T1D to become active partners in their health and care.

The following hypotheses will be tested in two steps:

Adolescents with T1D who receive a structured, person-centred transition programme have a higher patient empowerment score than adolescents who receive usual care.A structured, person-centred transition programme is equivalent to a dedicated youth clinic in empowering adolescents with T1D.

## Methods and analysis

We have used the recommendations in the Standard Protocol Items: Recommendations for Interventional Trials reporting guidelines in this protocol paper.^19^

### Design and setting

An RCT is being conducted in two paediatric diabetes clinics in which patients are randomly assigned to either the intervention group (study arm 1) where they receive usual care plus the structured transition programme, or to the control group (study arm 2) where they receive usual care only. In parallel, all patients followed up in a special youth clinic comprise study arm 3, to be compared with study arm 1 at a later stage. All the clinics are located at University Hospitals in Stockholm, Sweden. The number of transferred patients per year differs between the centres. For an overview of the three study arms, see figure 1.

**Figure 1 F1:**
[figure not shown]
Overview of the study design. RCT, randomised controlled trial; TC, transition coordinator.

### Participants and recruitment

Inclusion criteria for the study:

Literate, Swedish-speaking adolescents with T1D.Aged 16 years.Diabetes duration >1 year.If other diagnoses are present, T1D must be the primary diagnosis and not a side effect of other diagnoses or treatment for example, cystic fibrosis or cortisone-triggered diabetes.

Parents/guardians, as well as the adolescents, will be asked to participate, the inclusion criterion being that they are literate and Swedish speaking. Participants will be excluded if they are diagnosed with conditions affecting cognitive abilities and may have difficulties understanding and/or completing questionnaires.

A transition coordinator (TC) will contact 16-year-old adolescents eligible for inclusion in the RCT (study arm 1 and 2) during scheduled outpatient visits or by telephone. The adolescents and their guardians will be informed both verbally and in writing about the purpose of the study, its voluntary nature, the right to cease participation at any time, the data storage procedure and the strict anonymous processing of data. In the youth clinic (study arm 3), a data collection officer (DCO) will handle recruitment and data collection.

At both RCT centres, participants are assigned to either the intervention or the control group. This is done with a web-based randomisation system (1:1) employing stratified block randomisation with a random variable block size. Block randomisation ensures that the TCs in the two centres have relatively continuous exposure to the intervention over time, allowing them to keep their skills up to date and to ensure the fidelity of the intervention. The fact that the block sizes vary randomly minimises the possibility of the TCs being able to predict group assignments. Stratification is made by the centre to achieve an equal distribution of patients in the intervention, with control groups at both centres. Furthermore, stratification for sex and glycated haemoglobin (HbA1c) is crucial to ensure the distribution in the groups due to the knowledge that female adolescents have poorer glycaemic control compared with males, and that adolescents with unsatisfactory glycaemic control are a high-risk population.^20 21^ The grouping for HbA1c is based on ISPAD (International Society for Pediatric and Adolescent Diabetes) guidelines 2014.^20^ Overall, this approach decreases the within-centre variability and reduces the risk of bias and confounding.^22^An intention-to-treat principle will be used.

### Intervention

#### Transition programme (intervention group)

A multicomponent intervention, adapted from the brief transition programme of Hilderson *et al*^23^ and the STEPSTONES-CHD project,^16^ will be implemented. This transition programme comprises eight key components: (1) a TC; (2) a person-centred written transfer plan; (3) provision of information and education about T1D and treatment, health behaviours, dealing with school, friends, leisure activities and the importance of treatment adherence; (4) high access to the TC via telephone/sms; (5) information about and contact with the adult diabetes care team; (6) meeting with other young people with T1D; (7) support for and guidance of parents and (8) the actual transfer to the adult diabetes outpatient clinic. The components are implemented in five steps: (1) first visit with TC at the diabetes paediatric outpatient clinic at the age of 16 years; (2) second visit with TC at the diabetes paediatric outpatient clinic at the age of 17 years; (3) ‘adolescent day’ group information with parents and adolescents, with the participation of healthcare professionals from the adult outpatient clinic and young adults with T1D; (4) third visit with TC at the diabetes outpatient clinic at the age of 18 years and (5) the current transfer to one of the eight adult outpatient clinics that care for adults with T1D in the area (figure 1). The intervention is delivered by specialised trained paediatric nurses at the two paediatric diabetes outpatient clinics (study arm 1 and 2). The content of the patient education is adapted to T1D.

#### Usual care (intervention and control group)

The current usual care is provided to all participants, irrespective of whether they are randomised to the intervention or not. Usual care includes check-up visits to the paediatric diabetes outpatient clinic according to international, national and local guidelines every third months, with adjustments for individual needs.^24 25^ Visits include a meeting at the paediatric diabetes outpatient clinic with a nurse or a physician and it is up to each family if the parents attend these visits. In the area, there are several adult diabetes outpatients’ clinics to be transferred to. In one of the two intervention clinics usual care includes that adolescents planned to be transferred to the adult diabetes outpatient clinic in the same hospital will be scheduled for a transfer visit in groups. If an adolescent does not participate in this group referral, the same routines apply as for the rest of the adolescents in the control group, that is, they will be referred directly to the chosen adult diabetes clinic. None of the two intervention centres has a formal TC in place and no additional transfer preparation.

#### Youth clinic

At the dedicated youth clinic (study arm 3), adolescents with T1D will be followed up from 13 years of age and a more flexible transfer to adult care at 19–20 years of age will be applied. Usual care in this clinic includes visits to the diabetes nurse or the physician at the unit every second to third month with closer visits if needed, according to the patient’s glycaemic control. Midwives and social workers are employed at the unit and, if needed, visits to these can be arranged. The midwives provide advice on birth control, STDs (sexually transmitted diseases) and consultations in case of pregnancy. In the case of medical abortion, this can be performed in the youth clinic in a youth-friendly environment. No formal TC is in place, nor a formalised transition/transfer plan.

### Intervention fidelity

The special training of TC together with their experience of working with children and adolescents with T1D will ensure compliance that the components are implemented in line with the developed intervention. Prior to the start of this study, the TCs received 5 days of training including: adolescent psychosocial development and health with focus on chronic diseases in general and T1D in particular; PCC and empowerment; common neuropsychiatric diagnoses; the legal and human rights of young people. Moreover, they received training in communicating and interviewing young people using the psychosocial interview guide HEEADS, the acronym standing for home, education/employment, activities, drugs, sexuality and suicide/depression. The method uses structured questions to facilitate communication and create a sympathetic, confidential, respectful environment.^26^ The TC training was provided by experts within each field. TCs were also introduced to the administrative parts of the study in line with Good Clinical Practice (GCP) and have participated in a course in GCP.

Standard operating procedures (SOPs) were developed to ensure consistency throughout the study. These SOPs include ethical approval, study preparation and study administration, participant recruitment and survey completion; usual care, data storage, entry and security, study progress, process evaluation and publication policy. The Medical Research Council guidance on process evaluation of complex interventions is applied to monitor intervention fidelity.^27^ Acceptability, adherence/ﬁdelity and attrition are monitored using specific assessment forms; enrolment/follow-up form, and intervention implementation form to secure intervention delivery. These are ﬁlled out by the TCs during the entire intervention period. Qualitative interviews after completed delivery of the intervention will provide insights into the context of the intervention and the mechanisms of impact, based on the experiences of participants.

To avoid contamination, the TCs will not care for adolescents from the control group or adolescents eligible for the study, and team members at the outpatient clinic who are not involved in the study will only be given a brief outline of the intervention programme content.

### Data collection

Baseline data will be collected when participants (the adolescent and one or two parents) have agreed to participate in the study. Participants are asked to complete the set of pen-and-paper questionnaires at 16, 17 and 18.5 years of age (figure 1). These are sent by post to the participants’ home address before the next scheduled outpatient visit. The pack contains an instruction letter, a set of questionnaires and a prepaid and addressed reply envelope. Baseline data (T0) will be collected before any intervention is started (study arm 1). For T0, the most recent HbA1c value before inclusion in the study will be used. It is estimated that the questionnaires will take approximately 30 min to complete. Participants will be asked to complete the set of questionnaires themselves and to return them within 3 weeks. If the questionnaires are not returned within this time frame, patients will be reminded by a new set of questionnaires or asked to complete them while waiting in the waiting room at the next visit.^16 28^

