**Transfer specific**			
Transition readiness	Readiness for Transition Questionnaire^38^	T0, T1, T2	A+P
Uncertainty (parents)	Uncertainty Scale (Linear Analogue Scale)^39^	T0, T1, T2	P
Clinical indicators	Clinic attendance rates, pretransfer and post-transfer Time between last visit in PC and first visit in AC	T2	Admin
Transitional Care Experiences Questionnaire	In progress	T2	A

A, adolescents; AC, adult care; CGM, continuous glucose monitoring; CSII, continuous Ssubcutaneous Iinsulin Iinfusion; HbA1c, glycated haemoglobin; isCGM, intermittent scanning continuous glucose monitoring; MDI, multiple daily injection; NDR, National Diabetes Registry; p, parents; PC, paediatric care; SMBG, self-monitoring blood glucose testing.

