#### Transfer specific

The Readiness for Transition Questionnaire (adolescent and parent version) examines two aspects. First, the overall transition readiness is assessed, using two items ranging from 1 to 4. The sum of these two items results in a score ranging from 2 to 8. Second, the frequency of adolescent responsibility and parental involvement are reported for 10 different health behaviours on a four-point Likert scale. Each variable results in a total score ranging from 10 to 40, with higher scores indicating higher adolescent responsibility or parental involvement, respectively.^38^

Parental uncertainty is measured using a 10 cm Linear Analogue Scale (LAS) with the end points ‘not uncertain at all’ (=0) and ‘extremely uncertain’ (=100). Parental uncertainty comprehends parents’ perceptions of certainty/uncertainty prior to their child’s transfer to adult care. This LAS was developed for an ongoing study in the STEPSTONES-CHD project and has been used in a cross-sectional study.^39^

The new questionnaire on transfer and transition experiences is under construction and will be tested on young persons aged 19–21 years with long-term conditions and experience of the transfer to adult care in order to evaluate its psychometric properties.

Clinical indicators, such as attendance for scheduled outpatient visits before and after transfer to adult clinic and the duration between last visit in paediatric care and the first in adult care, will be collected from the medical record.

Information about validity, reliability and responsiveness of the questionnaires is provided in a online supplementary file.^29 32–35 37–40^

10.1136/bmjopen-2019-036496.supp1Supplementary data

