### Data analysis

The primary endpoint (total score of the level of empowerment at T2) will be analysed using Fisher’s non-parametric permutation test unadjusted between the intervention group and the control group in the RCT on the Full Analysis Set with imputation of missing values using stochastic imputation. A sensitivity analysis will be conducted with analysis of covariance (ANCOVA) adjusting for stratification variables without imputation. If confounders are found, complementary analyses will be conducted using ANCOVA between the two groups adjusted for these confounders. A confounder is a baseline variable that differs between the groups and influences the primary outcome variable. For comparison between the two randomised groups, Fisher’s non-parametric permutation test will be used for continuous variables, Fisher’s exact test for dichotomous variables, Mantel-Haenszel X^2^ test for ordered categorical variables and Pearson X^2^ test for non-ordered categorical variables. Missing data will be handled with stochastic imputation. Mean difference between the two groups with 95% CI will be presented for all continuous and dichotomous variables. For comparison within groups, Fisher’s non-parametric permutation test for paired observation will be used for continuous variables and Sign test for dichotomous variables and ordered categorical variables.

All analyses will be predefined in a detailed statistical analysis plan before data base lock. In a later stage, a comparison between the intervention group and a youth clinic group (study arm 3) will also be performed. All significance tests will be two sided and conducted at the 5% significance level.

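### The unit of analysis for parent-reported secondary outcomes is not fixed: one or two parents may answer per randomised adolescent, and the only stated rule for continuous outcomes is an unadjusted permutation test

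*Protocol article*

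**What the plan says.** All references are to the protocol article.

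- **Who answers.** Data collection: "Baseline data will be collected when participants (the adolescent and one or two parents) have agreed to participate in the study". These participants receive questionnaires when the adolescent is 16, 17 and 18.5 years old. Participants and recruitment confirms that parents or guardians are themselves invited to take part.
- **Which outcomes are parent-reported.** Transfer specific: "The Readiness for Transition Questionnaire (adolescent and parent version) examines two aspects", and "Parental uncertainty is measured using a 10 cm Linear Analogue Scale (LAS"). Table 1 lists transition readiness with adolescents and parents as sources, and the uncertainty scale with parents as the only source. Both are secondary outcomes.
- **What is randomised.** Design and setting: "patients are randomly assigned to either the intervention group (study arm 1") or to the control group. Stratification is by centre, sex and HbA1c.
- **How groups are compared.** Data analysis: "For comparison between the two randomised groups", Fisher's "non-parametric permutation test will be used for continuous variables". A mean difference with a 95% CI accompanies each continuous variable. No separate rule is given for parent-reported outcomes. Adjustment for the stratification variables appears only in a sensitivity analysis of the primary endpoint.
- **What is deferred.** The same section leaves full detail to a statistical analysis plan, to be completed before database lock. It is not available here.

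**The concern.** A permutation test takes its validity from re-assigning the units that were actually randomised. Two parents of the same adolescent share one allocation, and their answers about that adolescent are likely to be correlated. They are therefore not exchangeable one by one between arms.

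The article describes a data structure with one or two parent records per adolescent. It pairs this with one blanket test that names no unit. The two fit together only with a further rule, either reducing each family to one value or modelling the family.

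Without that rule, an analyst could apply the test directly to parent records. The reference distribution would then be too narrow, and the p-value and confidence interval too optimistic. Families with two responders would also count twice in the mean. Parental uncertainty is the most exposed outcome, because it has no adolescent version to set beside it.

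**Working it through.** **Inputs from the article.** Adolescents are randomised 1:1. The target is 5.25 points, stated to be 0.5 SD, so SD = 5.25/0.5 = 10.5. Alpha is 0.05 two-sided, power is 80%, and dropout is 10%. There are one or two parents per adolescent.

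**Inputs not in the article, so assumed.** The share s of families with two responding parents is taken from 0.25 to 1. The within-family correlation rho is taken from 0.1 to 0.7.

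**Step 1: the plan's own figure.** n per arm = 2(1.960 + 0.842)² / 0.5² = 62.8, rounded up to 63. Allowing for dropout, 63/0.90 = 70. Both match Proposed sample size. The calculation concerns the adolescent's own empowerment score, one value per patient, so the parent question does not touch it.

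**Step 2: design effect if each parent were a separate observation.** An average family contributes 1 + s records. The variance of the mean, relative to independent records, is

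DE = [(1 − s) + 2s(1 + rho)] / (1 + s).

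The naive standard error is 1/√DE of the true one. A nominal 5% test has actual size 2[1 − Φ(1.96/√DE)].

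Worked example, s = 0.5 and rho = 0.5: DE = (0.5 + 1.5)/1.5 = 1.33; 1.96/√1.33 = 1.70; size = 9.0%.

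| s | rho | DE | naive/true SE | actual size |
|---|---|---|---|---|
| 0.25 | 0.1 | 1.04 | 0.98 | 5.5% |
| 0.25 | 0.5 | 1.20 | 0.91 | 7.4% |
| 0.5 | 0.3 | 1.20 | 0.91 | 7.4% |
| 0.5 | 0.5 | 1.33 | 0.87 | 9.0% |
| 1 | 0.3 | 1.30 | 0.88 | 8.6% |
| 1 | 0.5 | 1.50 | 0.82 | 11.0% |
| 1 | 0.7 | 1.70 | 0.77 | 13.3% |

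**Step 3: check on the permutation test itself.** A permutation test does not use a standard error directly, so the normal approximation was checked by simulation under the null (63 families per arm, 1,500 replicates, 499 permutations each).

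| s | rho | permuting individual parents | permuting one mean per family |
|---|---|---|---|
| 0.5 | 0.5 | 8.3% | 4.5% |
| 1 | 0.3 | 8.0% | 4.0% |
| 1 | 0.5 | 9.9% | 4.7% |
| 1 | 0.7 | 12.7% | 4.6% |

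The simulation error around 5% is √(0.05 × 0.95/1500) = 0.56 percentage points. The family-level results are therefore compatible with the nominal level. The individual-level results track the formula and lie well above 5%.

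**The case against.** The strongest reply is that the article contains no error, only silence. No sentence makes each parent a separate observation. The test is stated for a comparison of the randomised groups, and the randomised units are adolescents. One parent value per adolescent fits that text equally well and gives a valid test. How two questionnaires become one value is a derivation rule that a condensed article may leave to the analysis plan.

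Most of this stands. A reader might infer that the plan already treats parents as independent, so that the parent results will have standard errors that are too small. The documents do not support that reading: the inflation is conditional on a parent-level analysis that the article neither states nor excludes.

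It is also fair that the size rests wholly on assumed inputs. Two responders in every family is the extreme case, and at the mild end the inflation is negligible (5.5%). Adjustment for baseline and strata does not address clustering and is a separate improvement.

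What does not stand is that there is nothing to act on. The article itself fixes both a structure of one or two parents and a blanket unadjusted test. Applied literally to the records as collected, that test would permute units that are not exchangeable.

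**Conclusion.** The point holds as a conditional one. The article allows one or two parents per randomised adolescent but does not fix the adolescent or family as the unit for parent-reported outcomes. If both parents were entered separately, nominal 5% tests would run at about 5.5% to 13%, and intervals would rest on a standard error about 2% to 23% too small. These figures assume s from 0.25 to 1 and rho from 0.1 to 0.7; the article gives neither quantity. With one value per family the problem disappears.

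The scope is narrow: the parent Readiness for Transition Questionnaire and parental uncertainty, both secondary. A reader might extend the concern to the trial's main result. That would be wrong, because empowerment is one self-report per adolescent, and its test and the 63/70 per arm are unaffected.

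**What to change.** State in the analysis plan, before database lock, that the randomised adolescent (the family) is the unit for every parent-reported outcome. Then do one of the following:

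- Derive one value per adolescent and time point, either the mean of the available parents or a pre-specified index parent, and permute by family.
- Keep both parents' values and fit a mixed model with a family random effect.

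In either case, adjust for the baseline parent score and for centre, sex and HbA1c group. The baseline score is already collected and the strata are known from randomisation. Apply the same unit to the confidence intervals and to the within-group paired comparisons. State too that a family with only one participating parent is not missing a second value, so that the stochastic imputation does not create one. Report the number of families with two responders in each arm.

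The cost is wording only. Data collection, sample size and the primary analysis do not change.
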